**Fig. 1 Fig1:**
[figure not shown]
SPIRIT figure highlighting the proposed timeline of the intervention and assessments

### Data collection, management, and analysis

#### Data collection methods

The primary outcome measures are related to academic performance, well-being, and symptomatology, which will be collected at three time points: pre-intervention, post-intervention, and 1 month follow-up. Academic performance (math and reading comprehension) will be assessed with a sample of items taken from TIMSS (mathematics) and from PIRLS (reading comprehension) [27].

#### Measures administered

All the measures included in the current study are self-report questionnaires that have been selected after a careful review of the scientific literature for their appropriateness for being used with adolescents and young people as well as their validity and reliability.

##### Screening

The screening scale contains 26 items and target symptoms not covered by other scales in the instrument [28]. The first 22 items concern how much or how often participants have been affected by a series of situations in the two weeks before completion. The last four items cover substance use and suicidal thoughts, and participants are instructed to answer “Yes” or “No.”

##### Attention deficit hyperactivity disorder (ADHD)

To assess ADHD symptomology, the World Health Organization Adult ADHD Self-Report Scale (ASRS) [29] is used. It consists of six items, and, while it has been developed for adults, it is also suitable for use in adolescents. Participants are asked to indicate how often they have experienced certain situations for the first eight items and to indicate the approximate age when problems with organization, concentration, or impulsivity first occurred, if applicable, at the last item.

##### Depressive symptomatology

The PHQ-9-A Depression Scale (PHQ-A) [30] is the adolescent-adapted version of the Patient Health Questionnaire and contains ten items. Participants are instructed to rate on a scale of 0 to 4 how often they felt affected by certain problems and the extent to which these situations (if applicable) affected the respondent professionally, personally, or socially.

##### Anxiety

The anxiety rating scale [31] consists of eight items. Participants are asked to indicate on a scale from 0 to 4 how often they felt affected by certain problems and to rate the extent to which these situations (if applicable) affected the respondent professionally, personally, or socially.

##### Social anxiety

The Severity Measure for Social Anxiety Disorder (SMSAD 11–17) is a ten-item instrument for children and adolescents [32]. On a Likert-type scale from 0 to 5, participants are asked to indicate how often they experienced various emotions, thoughts, and behaviors in social situations.

##### Adverse childhood experiences

The Adverse Childhood Experiences Rating Scale employed in this study [33] is composed of two sections, totaling 19 statements. Participants are instructed to indicate the number of statements that accurately describe their situation growing up.

##### Posttraumatic stress

The Post Traumatic Symptom scale [34] consists of 37 items. The first part of the scale presents a series of 17 stressful situations and participants are asked to indicate whether they have been exposed to one or more of these events in their lifetime. The last 20 items refer to the individual's reaction after experiencing a stressful situation.

##### Bullying

Bullying will be assessed with the six items used in the World Mental Health Initiative [35]. The items refer to times when someone is intentionally hurt or scared by a peer in the school setting, on the Internet, and in close relationships.

##### Eating disorders

The NEDA Eating Disorder Screening Tool [36] is composed of 14 items. The first 11 items address different aspects of eating behavior and/or self-image. These contain multiple response options, with participants being guided to choose the one that suits them. The last three items refer to information about height, lowest weight in the last year, and current weight.

##### Social support

The Perceived Social Support Questionnaire [37] contains six items, measured on a five-point Likert-type scale, where 1 = Does not fit me at all and 5 = Fits me extremely well.

##### Seeking help

The Attitudes Toward Seeking Professional Psychological Help – Short Form [38] instrument assesses attitudes towards seeking specialized psychological help. It consists of ten items and participants are asked to express the extent to which they agree with the statements.

##### Mental health stigma

The Peer Mental Health Stigmatization Scale [39] assesses stigmatizing attitudes of people experiencing mental health problems. It is composed of 24 items and participants are asked to express the extent to which they agree with the items.

##### Social media engagement

Social Media engagement will be measured with the Social Media Engagement Questionnaire (SMEQ) [40]. The questionnaire contains 5 items measured on an 8-point Likert scale (0 = not one day; 7 = every day). Higher scores represent higher engagement with social media.

##### Digital addiction

Digital Addiction will be measured with the Digital Addiction Scale for Teenagers (DAST) [41]. This is a 10-item instrument measured on a 7-point Likert scale ranging from never to very often.

#### Statistical methods

Our study will consist of a multisite cluster randomized trial in which the unit of measurement is at student-level, while randomization takes place at the unit of assignment, at classroom-level. Consequently, it is a low bias cluster-level RCT with potential joiners (i.e., individuals not in intervention clusters at random assignment but who enter later) being excluded and scant possibility of “contamination” or “treatment spillover” to the control classrooms. Analyses will employ linear mixed model with individual-level repeated measures nested within classrooms, nested within schools. Adhering to WWC group design standards [42], the model will include indicators for each intervention period and interaction terms for assignment to the intervention group and the period associated with the intervention. We will also report on robust standard errors from our fitted models to adequately account for dependence within clusters.

Nevertheless, youth research, and especially youth mental health research, has unique challenges concerning data gathering. First, although we adhere to a strategic research design to reduce missing data, patterns of attrition relating to individual and cluster-level factors will be investigated, including links to social and health variables. Second, challenges in gathering parental consent after classroom-level assignment to experimental condition would yield higher number of leavers, which constitutes individual-level attrition [42]. If data is missing at random, our analytic choice will yield unbiased estimates of treatment effects [43]. If data is missing not at random, weighting and multiple imputation would be used. In line with WWC standards [42] for cluster-level assignment RCTs, we will employ regression imputation, maximum likelihood, or nonresponse weights to address missing values while providing evidence that the approach appropriately adjusts the standard errors for clustering.

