### Sample size

R version 4.2.2 for Windows (R Foundation for Statistical Computing, Vienna, Austria) was used for the sample size calculation in a linear mixed-effect model (sjstats package). The R statistical computing environment will also be used for future model fitting and evaluation.

We used appropriate methods for two-level-designs [25] to determine sample size requirements for a cRCT with 3 experimental groups, 4 classrooms per experimental condition, 22 participants per cluster. For our linear mixed-effects model, a sample size of approximately 88 participants per experimental condition for a total sample size of 264 was sufficient to achieve 80% power to detect an effect size of Cohen’s *d* = 0.4 at an alpha level of 0.05. A medium effect size was assumed based on previous work on digital mental health literacy interventions [26].

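### With 12 classrooms, 4 per arm, robust standard errors account adequately for clustering only with a small-sample correction and small-sample degrees of freedom, and the protocol names neither

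*Protocol article*

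**What the plan says.** The Statistical methods section of the protocol article makes the classroom the unit of assignment: "randomization takes place at the unit of assignment, at classroom-level". The analysis is to be a "linear mixed model with individual-level repeated measures nested within classrooms, nested within schools", and the treatment effect enters through "interaction terms for assignment to the intervention group and the period associated with the intervention". The section then adds: "We will also report on robust standard errors from our fitted models to adequately account for dependence within clusters".

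The Sample size section gives the number of clusters: "cRCT with 3 experimental groups, 4 classrooms per experimental condition, 22 participants per cluster". The Assignment to study group section says that classrooms are allocated by simple randomization without stratification.

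The article does not say which robust estimator is meant, whether it is corrected for few clusters, or which reference distribution is used. A later sentence in Statistical methods does ask that standard errors be properly adjusted for clustering, but it concerns only the methods for missing values.

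**The concern.** The cluster sandwich variance is justified as the number of clusters grows large. Here each pairwise comparison of arms rests on 4 against 4 classrooms. Two things go wrong with the ordinary form at that number. The variance estimate is biased low, because residuals are taken around an arm mean fitted to the same four classrooms. The normal reference, or a t with one fewer degrees of freedom than the 12 clusters, also ignores how imprecisely that variance is estimated.

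Both errors act in the same direction: intervals are too narrow and tests reject too often. The trial has three arms and several primary outcomes (academic performance, well-being, symptomatology), so a robust test with twice or more its nominal error rate could readily support a false claim of benefit. The protocol does not merely leave the method open. It says that the remedy is adequate, and for its own number of clusters that depends on details it does not give.

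**Working it through.** **Inputs.** From Sample size: K = 4 classrooms per arm, 3 arms, m = 22 students per classroom, alpha 0.05. Sidedness is not stated; two-sided is assumed. The design figures agree with each other: 4 × 22 = 88 per arm and 3 × 88 = 264. The article gives no error rate for the robust test, so there is no stated figure to reproduce beyond the nominal 5%.

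**Bias of the sandwich.** In a balanced comparison of two arms with K classrooms each:
- Uncorrected sandwich (CR0): expected variance is (K − 1)/K = 3/4 of the true value, 25% too low. The standard error is √0.75 = 0.866 of its proper size.
- With the usual factor G/(G − 1) = 12/11 (CR1): 0.75 × 12/11 = 0.818, 18% too low. The standard error is 0.905 of its proper size.
- Bias-reduced sandwich (CR2): ratio 1.

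**Rejection rate.** With the correct variance ratio, the contrast divided by its estimated standard error follows a t distribution with 2(K − 1) = 6 degrees of freedom. With variance ratio r and critical value c, the rejection rate is P(|t₆| > c√r).

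| Estimator | Reference | c√r | Rejects at nominal 5% |
|---|---|---|---|
| CR0 | normal | 1.960 × 0.866 = 1.697 | 14.1% |
| CR0 | t, 11 df | 2.201 × 0.866 = 1.906 | 10.5% |
| CR1 | normal | 1.960 × 0.905 = 1.773 | 12.7% |
| CR1 | t, 11 df | 2.201 × 0.905 = 1.991 | 9.4% |
| CR2 | normal | 1.960 | 9.8% |
| CR2 | t, 6 df | 2.447 | 5.0% |

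**Interval width.** Relative to CR2 with 6 df, the 95% interval is 1.991/2.447 = 0.81 as wide with CR1 and t(11), and 1.697/2.447 = 0.69 as wide with CR0 and the normal reference. That is 19% to 31% too narrow.

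**Check by simulation.** Student-level data were simulated under no effect, with 12 classrooms × 22 students × 3 periods and an assumed intraclass correlation (ICC) of 0.01 to 0.10. Rejection was 13.5–15.0% (CR0, normal), 12.2–13.6% (CR1, normal), 9.3–9.9% (CR1, t 11) and 4.7–5.4% (CR2, t 6). The result hardly depends on the ICC.

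**Unequal arms.** Under simple randomization of 12 classrooms, an exact 4/4/4 split has probability 12!/(4!)³/3¹² = 34,650/531,441 = 6.5%. In a class-mean simulation with at least 2 classrooms per arm, CR0 with a normal reference rejected 17%, CR1 with t(11) 12%, and CR2 with a fixed 6 df 7%. The degrees of freedom should therefore come from the realised allocation.

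**The model-based test, conditional on assumptions.** A classroom intercept that is constant over time cancels from change since baseline. Suppose the mixed model has no classroom-by-period term and classrooms drift differently. With total variance 1, take classroom-by-period variance v_c = ICC × (1 − classroom autocorrelation) and student-level variance v_e = (1 − ICC) × (1 − student autocorrelation). The true variance of the arm-by-period contrast then exceeds the model's variance by the ratio (v_c + v_e/m)/((v_c + v_e)/m). At ICC 0.05, classroom autocorrelation 0.8 and student autocorrelation 0.7, all assumed:
- v_c = 0.05 × 0.2 = 0.010 and v_e = 0.95 × 0.3 = 0.285
- ratio = (0.010 + 0.285/22)/(0.295/22) = 0.02295/0.01341 = 1.71
- rejection = P(|Z| > 1.96/√1.71) = 13.4%

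Over ICC 0.05–0.10, classroom autocorrelation 0.8–0.9 and student autocorrelation 0.5–0.7, the range is 7.6% to 21.0%. At classroom autocorrelation 1.0 it falls to 5%.

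**The case against.** **The estimator is not named, and such detail belongs in an analysis plan.** The quoted sentence is compatible with CR2 and Satterthwaite degrees of freedom, which R, the stated software, can supply. The analysis plan is not shown. This stands as far as it goes: the article does not commit to an anti-conservative estimator, so the 9–14% is conditional on the ordinary form being used. But the sentence goes beyond leaving a detail open, because it asserts adequacy, and the plain reading of robust standard errors is the ordinary sandwich.

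**The robust errors are supplementary.** They are to be reported alongside a mixed model with classroom and school levels. This also stands. A reader might infer that the trial's main test has a 9–14% error rate; the article does not support that. In the class-mean simulation, a pooled classroom-level test held about 5% with 9 df, and about 8% with a normal reference.

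**The mixed model may be adequate.** A reader might infer that it fails too. The article gives the nesting levels but does not say that the only random effects are intercepts, and it gives no ICC or autocorrelation. The 8–21% range rests on all of these as assumptions and disappears if classrooms do not drift. It is a reason to specify the random effects, not a demonstrated error. If the model does omit drift, classroom-clustered robust errors are a sensible complement; their defect is then only the small-sample one.

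**Clustering by school.** A reader might argue that there are fewer independent units still. The article places assignment at the classroom and does not give the number of schools, so this is not supported.

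**The trial is called exploratory.** That softens the consequences but does not make the intervals correct.

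**Conclusion.** The point holds in conditional form. With 4 classrooms per arm, the statement that robust standard errors deal adequately with clustering is true only with both a bias correction and small-sample degrees of freedom, and the article states neither. Under the ordinary sandwich, robust tests at a nominal 5% reject about 9% (CR1, t 11) to 14% (CR0, normal). CR2 alone, with a normal reference, leaves about 10%; CR2 with 6 df gives 5.0%. These figures assume two-sided tests and the planned 4/4/4 split. They need no assumption about the ICC, and unequal arms make them worse.

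The finding concerns the robust tests and intervals. It does not show that the model-based test is wrong, although a mixed model without classroom-by-period variation would also be anti-conservative for the arm-by-period effect if classrooms drift differently over time, by an amount that depends on correlations not given in the article.

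**What to change.** Replace the general statement with a named small-sample method:
- Report robust standard errors in bias-reduced form (CR2), clustered at classroom, with Satterthwaite degrees of freedom computed from the classrooms actually allocated to each arm.
- Base mixed-model inference on Kenward-Roger or Satterthwaite degrees of freedom, and include a classroom-by-period random effect.

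This changes the analysis text only. Standard R packages provide these methods, and recruitment and trial conduct are untouched. The cost is wider intervals: with a 4/4/4 split, CR2 with 6 df gives a 95% interval 1/0.81 = 1.23 times as wide as CR1 with t(11), and 1/0.69 = 1.45 times as wide as CR0 with a normal reference.

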### Assignment to study group

The participants will be randomly assigned to one of the three trial arms (see Fig. 1). Randomization will be performed by a research assistant using a simple (unrestricted) randomization sequence that assigns one of three unique numbers (1, 2, or 3) per classroom enrolled in the intervention, signifying the experimental condition. No stratification will be employed. To conceal the allocation mechanism, the same research assistant will use sequentially numbered, opaque, sealed envelopes and will subsequently monitor the assessments and allow access to the application for the participants in the waitlist control group after 6 weeks. Two different research assistants will be responsible with enrolling the participants in the intervention and assigning them to the intervention by maintaining direct contact with student representatives from each classroom that is enrolled in the intervention. Neither the participants nor the psychologists involved in disseminating the intervention to the adolescents will be blinded, as blinding is not feasible given the context of the current trial. The principal investigator and the statisticians curating the dataset and running the data analysis will remain blinded to the study condition until the completion of the study.

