### Ethics and dissemination

This study is approved by the ethics commission at the University of Bucharest. Since the recipients of the intervention are minors, careful consideration has been given to obtaining informed consent from parents or legal guardians, while also properly informing the students about the contents of the intervention that they are enrolled in. Participant data will be confidential and stored on secured servers. Additionally, since we also collect mental health data, special attention will be given to any increase in symptomatology or any participants presenting harm to themselves. If such situations arise, they will be handled by the clinical psychologists in the research team. Any subsequent changes to the protocol will be updated on ClinicalTrials.gov.

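### Parental consent is gathered after classroom assignment with nothing shown to hide the arm from families, so the low-bias label and the missing-data remedies claim more than the design supports

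*Protocol article*

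**What the plan says.** All references are to the protocol article.

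- **Statistical methods, order of events.** The text states that "randomization takes place at the unit of assignment, at classroom-level". It then warns that "challenges in gathering parental consent after classroom-level assignment to experimental condition would yield higher number of leavers", "which constitutes individual-level attrition".
- **Statistical methods, bias.** The design is described in these terms: "it is a low bias cluster-level RCT". The same sentence mentions the exclusion of late joiners and the small chance of contamination.
- **Statistical methods, missing data.** "If data is missing at random, our analytic choice will yield unbiased estimates of treatment effects". For data missing not at random the text names weighting and multiple imputation. It also lists nonresponse weights, maximum likelihood and regression imputation, and promises to examine attrition patterns against individual and cluster factors.
- **Assignment to study group.** "Neither the participants nor the psychologists involved in disseminating the intervention to the adolescents will be blinded". Opaque sealed envelopes protect the classroom sequence.
- **Ethics and dissemination.** Parents or guardians consent, and care is taken over "properly informing the students about the contents of the intervention that they are enrolled in".

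**The concern.** In a cluster trial, randomisation makes the classrooms comparable. It makes the analysed students comparable only if entry to the analysis does not depend on arm. Here entry requires parental consent, and consent comes after assignment. The three offers differ visibly: an online programme, the same programme with facilitator contact, or a waitlist. A family that knows which one its child's class has drawn may decide differently for each.

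The plan excludes students who join late, which closes one route for selection after assignment. Refusal after assignment is the mirror image, and it is passed to missing-data methods. At stake is whether the students compared are still a randomised comparison. A bias of this kind does not shrink as the sample grows.

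**Working it through.** **1. Can the listed methods reach the students who are lost?** A student whose parents refuse presumably gives neither baseline nor outcome; the article does not say so outright.

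- A likelihood-based mixed model uses the records of students who have at least one. It borrows nothing from a student who has none.
- Regression or multiple imputation needs student-level predictors. None is described for non-consenters.
- Nonresponse weights could use classroom and school, which are known for everyone on the class list. They cannot adjust for differences between consenting and refusing families within a classroom.
- In standard form, all of these assume missingness at random given observed data. Naming weighting and multiple imputation for the other case does not make them valid there. No model or shift parameter for that case is described.

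**2. How large could the effect be?** The article gives no consent rates, so this is an illustration. It assumes that:

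- families consent when an unmeasured standard-normal trait exceeds a threshold, and a fraction p consents;
- the trait correlates ρ₁ with the post score;
- there is no true treatment effect.

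The mean trait among consenters is m(p) = φ(z_p)/p, and the spurious post-score difference is ρ₁ × [m(lower p) − m(higher p)].

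m(0.9) = 0.195; m(0.8) = 0.350; m(0.6) = 0.644.

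| Consent, ρ₁ = 0.3 | Difference in m | Post-score bias | Share of d = 0.4 |
|---|---|---|---|
| 80% v 60% | 0.644 − 0.350 = 0.294 | 0.3 × 0.294 = 0.088 SD | 0.088/0.4 = 22% |
| 90% v 60% | 0.644 − 0.195 = 0.449 | 0.3 × 0.449 = 0.135 SD (0.13 from unrounded values) | 0.135/0.4 = 34% |
| equal rates, same mechanism | 0 | 0 | 0 |

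The 0.4 is the effect size in the Sample size section. The sign depends on which arm consents less and on the sign of the correlation.

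**3. What does the planned model leave?** The model has arm-by-period interactions, so it estimates a difference in change. If the trait correlates ρ₀ with baseline, the bias in change is (ρ₁ − ρ₀) × [difference in m]. With ρ₁ = 0.3:

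| Consent | ρ₀ = 0.3 | ρ₀ = 0.1 | ρ₀ = 0 |
|---|---|---|---|
| 80% v 60% | 0 | 0.2 × 0.294 = 0.059 SD | 0.088 SD |
| 90% v 60% | 0 | 0.2 × 0.449 = 0.090 SD | 0.135 SD |

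A simulation at 90% v 70% consent agrees with this pattern. Its post-score bias was 0.09 SD, and its change-score bias was 0, 0.06 and 0.09 SD for ρ₀ = 0.3, 0.1 and 0. Motivation to engage is a trait that could plausibly relate more to later scores than to baseline.

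**The case against.** **Knowledge of the arm.** A reader might infer that parents are told the arm before they decide. The article does not say this. It gives the timing of consent, says that participants are unblinded, and says that students are informed about their intervention. This objection stands: the bias is possible, not established. What remains is that nothing described prevents it.

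**No analysis could repair it.** This too is stronger than the text allows. The arm-by-period contrast removes selection that is stable over time, and weights can use classroom and school. What remains is that the listed methods cannot be relied on, because no student-level source for non-consenters is described.

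**The attrition label.** The article takes its classification from a group-design standard that is not available here, and it openly treats consent loss as a problem to investigate. That is fair. Describing the pattern does not correct it, though, and the label does not alter how these students are lost.

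**Allocation concealment.** Because "the same research assistant will use sequentially numbered, opaque, sealed envelopes and will subsequently monitor the assessments", a reader might infer that the sequence is exposed. The same section gives enrolment and assignment to two different assistants, and preparing sealed envelopes is not in itself a breach. The point about consent does not rest on this.

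**The low-bias phrase.** Its sentence refers to joiners and contamination, not to consent. So it needs qualifying, and need not be withdrawn altogether.

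**Exploratory trial.** The article calls the trial exploratory, which lowers the stakes but does not make the comparison less open to selection.

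**Conclusion.** The concern holds in conditional form. The article places parental consent after classroom assignment, treats refusal as attrition, and describes nothing that hides the arm from unblinded families. If consent depends on arm, the analysed groups can differ by selection that the named methods cannot be relied on to correct. The unqualified low-bias label is therefore not supported, and the remedy named for data missing not at random does not fit that problem.

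Under the assumed consent rates, a correlation of 0.3 with the post score, and a baseline correlation between 0 and 0.3, the bias in the planned contrast lies between 0 and about 0.09 SD (80% v 60%) or 0.13 SD (90% v 60%). It is 0 if consent does not depend on arm. Equal consent rates alone would not prove this, since different kinds of family could consent in each arm. The article does not support saying that the bias is present, or which way it runs.

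**What to change.** 1. **Classrooms not yet assigned.** Complete parental consent, student assent and the baseline assessment before the classroom's arm is revealed, and fix the analysis roster at that point. The Trial status section says that recruitment has begun and gives only an estimated completion date, so this may still be possible for some classrooms. The cost is a short wait per classroom and a changed order of steps across schools.
2. **Classrooms already assigned.** Report the numbers invited and consented, and the baseline characteristics of those who consented, by arm and classroom. The cost is record-keeping. An analysis limited to students who consented before assignment would add little, since these classrooms would contain few or none.
3. **Missing-data text.** Replace the sentence on data missing not at random with an explicit sensitivity analysis, such as a delta adjustment. If non-consenters in an arm with consent fraction p differ from consenters by δ, that arm's mean moves by (1 − p) × δ. Arm-specific δ values can then be varied over a stated range. The cost is analysis time.
4. **Bias statement.** Limit the low-bias wording to joiners and contamination, and state that selection at consent remains possible. This costs nothing.

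The envelope holder should stay as described: the other assistants named enrol participants, and giving them the envelopes would weaken the present separation.

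### At least some parental consent appears to follow classroom assignment, so entry to each arm can depend on the arm; the planned missing-data methods can correct this at most in part

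*Protocol article*

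**What the plan says.** All references are to the protocol article.

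- **Unit.** Statistical methods states that "randomization takes place at the unit of assignment, at classroom-level".
- **Timing of consent.** The same section expects that "challenges in gathering parental consent after classroom-level assignment to experimental condition would yield higher number of leavers". It classes these students as individual-level attrition under the standard it cites. No section places parental consent before assignment.
- **Claim about bias.** The section concludes: "Consequently, it is a low bias cluster-level RCT with potential joiners" being left out of the trial.
- **Handling.** Attrition patterns will be examined. The mixed model is taken to be unbiased if data are missing at random. Weighting and multiple imputation are named if they are not. Regression imputation, maximum likelihood and nonresponse weights are also listed.
- **Who knows the arm.** Assignment to study group says: "Neither the participants nor the psychologists involved in disseminating the intervention to the adolescents will be blinded". Blinding is promised for others: "The principal investigator and the statisticians curating the dataset and running the data analysis will remain blinded to the study condition". Sealed envelopes conceal the number drawn for each classroom.
- **Enrolment staff.** The same section says: "Two different research assistants will be responsible with enrolling the participants in the intervention and assigning them to the intervention", through contact with student representatives.
- **Information given.** Ethics and dissemination provides for parental consent and for "properly informing the students about the contents of the intervention that they are enrolled in", without giving the timing.

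**The concern.** Randomising classrooms makes the class rosters comparable between arms. It does not make the consenting subsets comparable if consent is decided after the arm is set and can be influenced by it. A family offered a programme with facilitator contact, a programme alone, or a wait may agree at different rates or for different reasons.

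The plan sees the problem but treats it as ordinary missing data. Never-consenters differ from dropouts because the trial never holds any data on them. If their absence depends on the arm and is related to how students would change over time, each between-arm contrast, including automated against blended, carries a bias that more participants would not shrink. The low-bias description would then not be supported by the procedure in the same section.

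**Working it through.** The plan gives no consent rate and no figure for this bias, so there is nothing of its own to reproduce. The planned effect of d = 0.4 (Sample size) serves only as a yardstick.

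**Step 1: order of events.** Statistical methods puts parental consent, for at least some students, after classroom assignment. Auditing lists checks of consent and of randomisation for each participant but gives no order, so it does not contradict this. The envelopes protect the draw for the classroom; nothing described conceals the arm at a later consent step.

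**Step 2: what each safeguard can reach.** Apart from the academic test items, the measures are self-report questionnaires (Measures administered; Data collection methods). A student without consent completes neither.
- Mixed model: there is no record at any time point, so the student does not enter the likelihood.
- Student-level imputation: there is no baseline or outcome to impute from.
- Nonresponse weights: these can adjust for whatever is known about everyone on the roster. The plan names no such source, and standard weights assume that non-consent is explained by the data used.
- Weighting and multiple imputation as the remedy for data missing not at random: in standard form both assume missingness at random given observed data.
- Excluding joiners: this controls later entry, not refusal within the original roster.

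**Step 3: which selection biases the contrast.** The model has a pre-intervention measurement and arm-by-period interactions. A stable difference in level between consenters in different arms is largely absorbed. What remains is selection related to change in the outcome.

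**Step 4: illustrative size.** Assume consent occurs when a standard normal propensity exceeds a threshold, and that this propensity correlates r with outcome change. The mean propensity among consenters at consent rate p is φ(z)/p, where z is the threshold.

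| p | φ(z)/p |
|---|---|
| 0.60 | 0.644 |
| 0.70 | 0.497 |
| 0.80 | 0.350 |
| 0.85 | 0.274 |

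Bias = r × difference in φ(z)/p, with r assumed to be 0.2 to 0.4:
- 80% vs 70%: 0.497 − 0.350 = 0.147; bias 0.03 to 0.06 SD.
- 80% vs 60%: 0.644 − 0.350 = 0.294; bias 0.06 to 0.12 SD.
- 85% vs 60%: 0.644 − 0.274 = 0.370; bias 0.07 to 0.15 SD.

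Against 0.4, this runs from 0.0294/0.4 = 7% to 0.148/0.4 = 37%. The comparison takes the SD of change as equal to the SD of the outcome. Since the SD of change is √(2(1 − ρ)) outcome SDs, that is exact when the pre-post correlation ρ is 0.5.

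**Step 5: boundary cases.**
- Equal consent and equal r in both arms: the bias is 0.
- Equal 80% consent, with selection in one arm only (r = 0.3 against 0): 0.3 × 0.350 = 0.105 SD. Similar consent rates alone do not rule the problem out.
- Simulation with no true effect (4 classrooms of 22 per arm before consent, ICC 0.05, an unmeasured trait driving both consent and outcome beyond baseline): adjusting for baseline among consenters left 0.05 to 0.12 SD in absolute value when selection differed between arms, and about 0 when it did not.

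**The case against.** The plan raises late consent itself, counts it as attrition under its cited standard, and promises to study attrition patterns. The trial calls itself exploratory, the waitlist also receives the application later, and the two active arms share their content, with facilitator contact offered as an option. These features may narrow differences in consent. All of this stands, and it limits the severity. It does not supply data on students who never consent.

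Four stronger readings are tempting, and the document does not support them.
- *Consent is collected by staff who know the arm.* The article does not say who approaches parents or what the form discloses. The enrolling assistants also assign, but they are described as working through student representatives. The sentence on informing students gives no timing. Knowledge of the arm at consent is likely, given the order and the unblinded participants, but it is inferred.
- *Every family decides after assignment.* The sentence is conditional and may describe late forms. It supports at least some, not all.
- *The named methods can repair nothing.* Weights built on roster data could adjust in part.
- *Any baseline imbalance in motivation or distress biases the effect.* Level differences are largely absorbed by the arm-by-period model.

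A separate analysis plan could add detail, but it could not recover questionnaires that were never completed.

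**Conclusion.** The concern holds in a limited form and should be fixed. On the document's own wording, at least some consent follows assignment in a trial with unblinded participants, so entry to an arm can depend on the arm. The named analyses cannot fully correct that, and the unconditional low-bias statement is not supported.

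This is a credible risk, not a demonstrated bias. The illustrated 0.03 to 0.15 SD rests entirely on assumed consent rates and correlations with change; neither is in the document. The direction is unknown. A reader might infer that the trial's contrasts are already invalid, but the article reports no consent data by arm from which to conclude that.

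**What to change.** - **Classrooms not yet assigned.** Use one arm-neutral consent and assent form that describes all three arms. Collect the forms, close the class list, and only then open that classroom's envelope. Define the analysis set as the students on the closed list.
- **Classrooms already assigned.** Report consent by arm, with the roster at assignment as the denominator. Compare results by consent timing only if enough classrooms per arm remain. With 3 × 4 = 12 planned classrooms, such a comparison may be uninformative or impossible.
- **Text.** Make the low-bias statement conditional on consent preceding assignment. State that imputation and weighting cannot fully correct arm-dependent non-consent.

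The cost is an ethics notification, the revised form and a short delay before each classroom starts, with no added participants. Trial status says that recruitment has begun, so the main change reaches only the classrooms still unassigned; their number is not given.
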